### Sample size

Regarding RTW, an OR of 2.0 between the Compensatory Cognitive Training–Supported Employment (CCT-SE) and CG is regarded as the smallest relevant clinical and societal OR. Thus, the required total sample size calculated using G*Power is 110 (i.e., 55 persons in each group; α = 0.05, power level of 0.80) [39]. With an estimated loss to follow-up of 15% [40], 125 participants will be required. On the basis of an ongoing TBI study [41], we assume that this will be achievable within 12–18 months. An OR of 2.0 is equivalent to a 33% absolute difference in employment status between the two groups. According to [name] et al. [21], 50% of patients attained competitive work at 12-month follow-up. If the proportion of employed patients in the CG is 50% at 12-month follow-up, the proportion for the intervention group in this study will be expected to be 83% or above on the basis of the given estimation.

Two strategic samples will be drawn for the process evaluation, comprising 40 cases from the intervention group and 20 from the CG. It is a goal to achieve a heterogeneous sample with variation in severity of TBI, sex, age, type of job and workplace, company size, industry, and sector.

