### Randomization

A permuted block randomization sequence will be generated by an independent statistician prior to the start of the trial. Eligible patients who consent to study participation will be randomly allocated in a 1:1 ratio in each block to receive either the study intervention or TAU (CG). An investigator who is independent of the patient screening process will be responsible for allocating the patients to the study conditions. Blinding of the patients and rehabilitation professionals is not possible, but the outcome assessors will be blinded to study allocation.

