### Trial status

This is protocol version 1.0. A feasibility study including six patients has been performed and concluded in July 2017. The results of the feasibility study are being prepared for publication. No major changes to the protocol were made as a result of the feasibility study. Recruitment and randomization of participants for the main study commenced in July 2017 and will end when we have enrolled the estimated sample size (approximately in November/December 2018).

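### Enrolling 125 leaves about 106 evaluable participants at the stated 15% loss, not the 110 required; 125 allows for only 12% loss

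*Protocol article*

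**What the plan says.** The Sample size section of the protocol article starts from an odds ratio of 2.0 for return to work and reports that "the required total sample size calculated using G*Power is 110 (i.e., 55 persons in each group; α = 0.05, power level of 0.80"). The next sentence moves from that number to the recruitment target: "With an estimated loss to follow-up of 15% [40], 125 participants will be required". No inflation formula is shown, and no other section gives a different target or loss rate.

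The Randomization section specifies 1:1 allocation within permuted blocks. The Trial status section says that recruitment "will end when we have enrolled the estimated sample size", and the Study setting section likewise ties the end of recruitment to the required sample size. Neither repeats the figure 125, but it is the only enrolment number in the document and the natural reading of both statements.

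**The concern.** An allowance for loss should make the number enrolled, less the expected loss, at least equal to the number needed for analysis. Here 125 less 15% falls below 110, so at least one of the three figures (110, 15%, 125) is wrong as written.

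This matters because the enrolment figure also closes recruitment. If it is followed, and attrition is what the plan expects, the 12-month comparison of the proportions back at work will have fewer participants than the plan calls required. Readers of the final report would also be misled about attrition: a loss of 13% or 14% would appear to be within the planned allowance while already leaving fewer than 110.

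**Working it through.** **Inputs, all from the Sample size section unless noted**

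- Evaluable total required: N = 110 (55 per group)
- Expected loss: d = 15%
- Enrolment target: 125
- α = 0.05 (sidedness not stated; two-sided assumed below), power 0.80
- Allocation 1:1 (Randomization section)

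**1. Trying to reproduce 125**

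- Standard inflation, N / (1 − d): 110 / 0.85 = 129.4, rounded up to 130. By group: 55 / 0.85 = 64.7, rounded up to 65, and 2 × 65 = 130.
- The incorrect shortcut, N × (1 + d): 110 × 1.15 = 126.5, rounded up to 127.

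Neither gives 125. The shortcut comes closer, but the document does not say how 125 was obtained.

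**2. Working backwards from 125**

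- Expected evaluable at 15% loss: 125 × 0.85 = 106.25, about 106 (53 per group).
- Shortfall against 110: about 4 evaluable, equivalent to 130 − 125 = 5 enrolled.
- Largest loss that still leaves 110: 1 − 110/125 = 15/125 = 12.0%.

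**3. What the shortfall costs in power**

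*(a) Taking 110 as giving exactly 80%.* The standardised effect scales with the square root of N:

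(1.960 + 0.842) × √(106/110) − 1.960 = 0.790, and Φ(0.790) = 78.5%.

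The loss is about 1.5 percentage points.

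*(b) Taking the effects named in the plan.* With a 50% control rate, an odds ratio of 2.0 means odds of 1 × 2 = 2, a rate of 2/3 = 66.7%. The plan also names 83% for the intervention group. Power is from the normal approximation for two proportions, two-sided 0.05, without continuity correction:

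| Comparison | 55 per group | 53 per group |
|---|---|---|
| 50% vs 66.7% (odds ratio 2.0) | 42.5% | 41.2% |
| 50% vs 83% | 96.6% | 96.0% |

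The drop from 55 to 53 per group is 1.3 points in the first row and 0.6 in the second.

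**4. A limit on what this check shows**

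The table also shows that 110 is not a verified requirement. The section states that "An OR of 2.0 is equivalent to a 33% absolute difference in employment status between the two groups", but 50% vs 83% has an odds ratio of (0.83/0.17) / (0.50/0.50) = 4.9. By the same approximation, 80% power needs 274 in total for an odds ratio of 2.0 from 50%, and 62 for 50% vs 83%. The 110 follows from neither. That is a separate and larger problem. The inflation step is wrong whichever effect was meant, because it uses only 110, 15% and 125.

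**The case against.** The best case on the other side accepts the arithmetic and disputes its weight. Five participants in 125 is 4%, and on every reading of the effect size the power lost is between about 0.6 and 1.5 points. No conclusion of the trial is likely to depend on that. Nor is 110 a sound benchmark, so falling short of it is a matter of internal consistency rather than evidence that the trial is too small by four people. Raising the target to 130 would correct the inflation step and leave an unsupported base.

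All of this stands as a limit on the size of the point. It does not make 125 the right figure for 110 at 15% loss, and nothing elsewhere in the document does.

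It can also be said that quoting power for 53 per group is not a simple correction, because the answer is 41% or 96% depending on which effect is meant. That is correct, and the fix takes account of it.

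Finally, 125 is odd and so cannot split equally under 1:1 allocation. This carries no weight: a 63/62 split is ordinary, and a blocked sequence may stop within a block.

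**Conclusion.** The concern holds. The plan's 125 does not yield 110 evaluable participants at 15% loss. It yields about 106 (53 per group) and is consistent with 110 only up to 12% loss. The figure that matches the plan's own 110 and 15% is 130.

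The practical effect is modest: about 4 evaluable participants, and about 1.5 points of power if 110 is taken to give exactly 80%. The counts rest only on the three figures in the Sample size section. The power figures also assume a two-sided test and a normal approximation. It remains worth correcting because it is a wrong figure in the headline design statement and governs when recruitment closes. The correction does not establish that 110 is adequate.

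**What to change.** Make the three figures agree in one of two ways.

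- **Keep 125 and restate the allowance.** For example: *125 participants will be enrolled; this retains 110 if loss is at most 12%, and about 106 (53 per group) are expected to be evaluable if loss is 15%.* This costs one sentence and no extra patients. If power is quoted for 53 per group, the effect size must be settled first, since the odds ratio of 2.0 and the 33-point difference lead to very different answers.
- **Keep 110 and 15%, and enrol 130 (65 per group).** This costs five more participants. At the recruitment pace the plan assumes (125 in 12 to 18 months, or 10.4 to 6.9 per month), that is about 0.5 to 0.7 of a month.

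The first is the proportionate choice while 110 itself is in doubt. If the base calculation is redone, the loss allowance should be applied to the new number by dividing by 0.85.

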To date, only a couple of randomized controlled trials (RCTs) have combined cognitive and vocational rehabilitation/SE for patients with mild to moderate TBI [20, 21]. The only study resembling our present protocol was performed by [name] et al. [21, 22]. Their 12-week compensatory cognitive rehabilitation intervention (Cognitive Symptom Management and Rehabilitation Therapy [CogSMART]) was offered in addition to SE for U.S. veterans with mild to moderate TBI. All participants were unemployed but wished to return to work. This group was compared with a control group (CG) that received enhanced SE only. Participants assigned to both SE and CogSMART demonstrated significant reductions in postconcussive symptoms and improvements in prospective memory, but there were no effects on RTW. The authors noted that their study was a pilot in need of replication. Moreover, a process evaluation was not performed in their study, and there are significant differences between the United States and Norway regarding the labor market as well as the welfare system. There is a need to explore different stakeholders’ experiences and processes at the workplace in the RTW process. Finally, there are no RCTs in which researchers have examined the cost-effectiveness of vocational rehabilitation following TBI.

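### The sample-size paragraph treats an OR of 2.0 as a 33-point difference (50% to 83%), which is an OR of 4.9; with 110 evaluable patients, power for OR 2.0 is about 42% (two-sided, 50% control rate), not 80%.

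*Protocol article*

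**What the plan says.** All the figures are in the Sample size section of the protocol article. An OR of 2.0 for return to work "is regarded as the smallest relevant clinical and societal OR". From this the section concludes that "the required total sample size calculated using G*Power is 110 (i.e., 55 persons in each group; α = 0.05, power level of 0.80"; allowing for 15% loss, it plans to recruit 125. It then translates the odds ratio: "An OR of 2.0 is equivalent to a 33% absolute difference in employment status between the two groups". The control rate is taken from the earlier pilot trial of cognitive training plus supported employment: "If the proportion of employed patients in the CG is 50% at 12-month follow-up", then "the proportion for the intervention group in this study will be expected to be 83% or above". The section states neither whether the test is one- or two-sided nor which G*Power procedure was used.

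Two other sections bear on the point. Statistical analysis specifies logistic regression for the proportion back at work at 12 months, so the odds ratio is the scale of the analysis. Background says of the pilot trial that "All participants were unemployed but wished to return to work", and that its comparison group received enhanced supported employment.

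**The concern.** The paragraph contains two different effects and calls them the same. OR 2.0 from a 50% control rate cannot reach 83%, and 110 patients is not the answer for either effect at 80% power.

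The proportion back at work at 12 months is the first primary outcome listed. A reader will take it that the trial has an 80% chance of detecting the smallest effect that matters. If the real chance is about half of that, a non-significant result could easily be taken as evidence against a relevant benefit when the design could not show one. The 83% figure also suggests that the smallest worthwhile gain is 33 points, about twice what OR 2.0 means.

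A lesser issue is the origin of the 50%. The pilot participants were unemployed and both of its arms had supported employment. Here everyone is employed at injury and controls receive usual care without the study's supported-employment programme, so the control rate may be quite different.

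**Working it through.** **Inputs (Sample size and Randomization sections):** α = 0.05; power 0.80; OR 2.0; control rate p₁ = 0.50; stated intervention rate 0.83; n = 55 per arm; 1:1 allocation. Assumption: two-sided unadjusted comparison of two proportions, with one-sided results also shown.

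**1. What OR 2.0 means on the risk scale.** p₂ = OR·p₁/(1 − p₁ + OR·p₁) = 2 × 0.5/(0.5 + 1.0) = 0.667. The difference is 16.7 points.

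**2. The largest difference OR 2.0 can produce.** p₂ − p₁ is greatest at p₁ = √2 − 1 = 0.414, where it is (√2 − 1)/(√2 + 1) = 0.172. No control rate gives 33 points.

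**3. What 50% versus 83% means as an odds ratio.** (0.83/0.17)/(0.50/0.50) = 4.88.

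**4. Trying to reproduce 110.** With p̄ = (p₁ + p₂)/2, the patients needed per arm are

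n = [1.96·√(2p̄(1 − p̄)) + 0.842·√(p₁(1 − p₁) + p₂(1 − p₂))]² / (p₂ − p₁)²

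- 50% v 66.7%: p̄ = 0.583, the square roots are 0.697 and 0.687, n = 136.2, rounded up to 137 per arm, **274 in total** (one-sided 216; two-sided with continuity correction 296).
- 50% v 83%: p̄ = 0.665, the square roots are 0.667 and 0.625, n = 30.9, rounded up to 31 per arm, **62 in total** (74 with continuity correction).

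The total of 110 is not reproduced from either effect.

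**5. Power with 55 per arm.** Power = Φ{[(p₂ − p₁)√n − 1.96·√(2p̄(1 − p̄))] / √(p₁(1 − p₁) + p₂(1 − p₂))}.

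- OR 2.0: (0.1667 × 7.416 − 1.96 × 0.697)/0.687 = (1.236 − 1.367)/0.687 = −0.19, so power is **42.5%**.
- 50% v 83%: the argument is 1.82, so power is **96.6%**.

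**6. Does the choice of test matter for OR 2.0 from 50%?**

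| Test, 55 per arm | Power |
|---|---|
| Pooled z, two-sided | 42.5% |
| Wald on log OR, two-sided | 42.2% |
| Pearson, exact enumeration | 42.1% |
| Fisher exact | 34.2% |
| Pooled z, one-sided | 55.2% |

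**7. Does the control rate matter?** For OR 2.0 with 55 per arm, two-sided:

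| Control rate | Intervention rate | Power |
|---|---|---|
| 20% | 33.3% | 35% |
| 30% | 46.2% | 41% |
| 40% | 57.1% | 43.5% |
| 50% | 66.7% | 42% |
| 60% | 75.0% | 39% |
| 70% | 82.4% | 33% |
| 80% | 88.9% | 25% |
| 85% | 91.9% | 20% |

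Over control rates of 10% to 90% in steps of 5 points, two-sided power never exceeds 43.5% and one-sided power never exceeds about 56%.

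**8. What 55 per arm can detect.** Solving the power formula for 80% with p₁ = 0.50 gives p₂ = 0.755: a difference of about 26 points, OR 0.755/0.245 = about 3.1.

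**9. Evaluable number.** 125 × 0.85 = 106, about 53 per arm; keeping 110 would need 110/0.85 = 129.4, so 130. With 53 per arm, power for OR 2.0 is about 41%, and the rate detectable with 80% power is about 76.0% (OR about 3.2).

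**The case against.** The strongest reply is that the 33% is a mislabelled relative figure: 66.7/50 = 1.33, so OR 2.0 from 50% is a 33% relative increase, which may then have been added to 50 as if it were absolute. The article does not say so, but it is plausible. It would explain the 83%; it would not repair the power claim, since 110 is still far short of 274.

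One could instead argue that the trial was really powered for 33 points. But the section derives 110 directly from OR 2.0, and for 33 points the power would be 97%, not the stated 80%.

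Some points do narrow the finding:

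- The 42% rests on a two-sided, unadjusted test and a 50% control rate. The article does not give the sidedness, and the planned logistic regression is adjusted.
- The calculation covers only the proportion back at work, not the other primary outcomes.
- The article makes the 50% conditional. That it may not transfer is fair comment, not an arithmetic error. The true rate could lie on either side: Background cites 13% to 85% across the literature, and entry requires sick-listing of at least 50% at two months. The lowest power figures need control rates of 80% to 85%, which the article does not assume.
- No section says a null result will be read as ruling out a relevant effect. That is a risk of the wording, not a stated intention.

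**Conclusion.** The concern holds. The equivalence of OR 2.0 with 33 points is mathematically impossible and needs no assumption to refute. The claim of 80% power for OR 2.0 is also wrong: about 42% with 55 per arm (two-sided, 50% control rate, unadjusted test), 55% if one-sided, and about 41% if 15% of the 125 recruited are lost. None of the control rates from 10% to 90% that were tried brings it near 80%, one- or two-sided. The figure of 110 also fails to match the 50% versus 83% comparison, for which it is larger than needed. This must be corrected, because it misstates what the trial can show on its first-listed primary outcome.

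**What to change.** Reword the Sample size paragraph without changing enrolment:

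- Delete the 33-point equivalence and the expectation of 83% or above. State that, from 50%, OR 2.0 means 66.7%: 16.7 points absolute, 33% relative.
- State that 55 evaluable per arm gives 80% power (two-sided 5%) for 50% versus about 76% (OR about 3.1, 26 points), and about 42% power for OR 2.0. If 125 are recruited and 15% lost, use 53 per arm instead: about 76.0% (OR about 3.2) and about 41%.
- State the sidedness and the test.
- Note that the 50% comes from an unemployed population and show power for OR 2.0 across control rates. The range should cover at least 50% to 85%; including lower rates would be more even-handed.
- Say that a non-significant result will not be read as excluding OR 2.0, and that the absolute difference will be reported with its confidence interval.

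The cost is a rewritten paragraph and a less favourable power statement; no extra patients are needed. Rewording makes the shortfall visible but does not remove it: 80% power for OR 2.0 would need about 274 evaluable patients, or 274/0.85 = about 323 recruited.

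### An OR of 2.0 is converted to a 33-point difference when it is 16.7 points at a 50% control rate, and the stated 110 participants fit neither effect

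*Protocol article*

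**What the plan says.** All the figures stand in one paragraph of the protocol article, under Sample size. An OR of 2.0 for return to work between the two arms "is regarded as the smallest relevant clinical and societal OR". From it the article concludes that "the required total sample size calculated using G*Power is 110 (i.e., 55 persons in each group; α = 0.05, power level of 0.80").

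It then translates the OR into percentages: "An OR of 2.0 is equivalent to a 33% absolute difference in employment status between the two groups". The control proportion is an assumption taken from the pilot trial on which the study is based: "If the proportion of employed patients in the CG is 50% at 12-month follow-up", then "the proportion for the intervention group in this study will be expected to be 83% or above on the basis of the given estimation".

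The Outcomes section lists the proportion back at work at 12 months among the primary outcomes. The Statistical analysis section compares it between groups by logistic regression. Under Randomization, patients are "randomly allocated in a 1:1 ratio in each block".

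**The concern.** A proportion of 50% is odds of 1. Doubling the odds gives odds of 2, which is two in three and not 83%. The translation therefore overstates the absolute effect by about a factor of two.

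These percentages are the only place where the article expresses its target effect on the scale that most readers use, and they stand beside the sample size derived from that effect. A reader who trusts the 33 points will think that 55 per group is ample. A reader who trusts the OR of 2.0 and checks it will find far less than 80% power. The paragraph does not let either reader see what the trial was sized to detect.

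**Working it through.** **Inputs, all from Sample size unless noted.** OR 2.0; control proportion p0 = 0.50; stated intervention proportion 0.83; alpha 0.05; power 0.80; 55 per group; 1:1 allocation (Randomization). The article does not say whether the test is one- or two-sided, so both were tried. Two-sided is the main case. The 55 are taken as patients analysed per group.

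**1. OR to proportion.** p1 = OR × p0 / (1 − p0 + OR × p0) = 2 × 0.5 / (0.5 + 1.0) = 0.667. The difference is 16.7 points.

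**2. The OR implied by 83% against 50%.** (0.83/0.17) / (0.50/0.50) = 4.88.

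**3. Could another control proportion rescue the sentence?** For an OR of 2.0 the difference is 2p0/(1 + p0) − p0. Its derivative, 2/(1 + p0)² − 1, is zero at p0 = √2 − 1 = 0.414. There the difference is 0.586 − 0.414 = 0.172, so 17.2 points is the ceiling. Conversely, a 33-point difference needs the smallest OR when the two proportions lie symmetrically about 50% (33.5% and 66.5%). That OR is (0.665/0.335)² = 3.94.

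**4. Trying to reproduce 55 per group.** The usual formula for two proportions, with p̄ the mean of p0 and p1, is

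n = [1.960 √(2p̄(1 − p̄)) + 0.842 √(p0(1 − p0) + p1(1 − p1))]² / (p1 − p0)²

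- 50% against 66.7%: (1.960 × 0.6972 + 0.842 × 0.6872)² / 0.1667² = 3.783 / 0.02778 = 136.2, so 137 per group (274 in total).
- 50% against 83%: (1.960 × 0.6675 + 0.842 × 0.6254)² / 0.33² = 3.366 / 0.1089 = 30.9, so 31 per group (62 in total).

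Other formulas (unpooled, arcsine, continuity-corrected) move these figures only a little:

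| Effect | n per group, two-sided | n per group, one-sided |
|---|---|---|
| 50% v 66.7% (OR 2.0) | 134–148 | 106–119 |
| 50% v 83% (OR 4.88) | 29–37 | 23–30 |
| OR 2.0, most favourable control proportion (pooled formula) | 133 | 104 |

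The stated 55 lies in none of these ranges.

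**5. Power with 55 per group, two-sided.** Power = Φ{[(p1 − p0)√n − 1.960 √(2p̄(1 − p̄))] / √(p0(1 − p0) + p1(1 − p1))}, with √55 = 7.416.

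- 50% against 66.7%: (1.236 − 1.367)/0.687 = −0.190, so power is 42%. It is at most 44% at any control proportion. One-sided, it is 55% at a 50% control proportion.
- 50% against 83%: (2.447 − 1.308)/0.625 = 1.82, so power is 97%.
- Solving for power 0.80 from a 50% control proportion gives p1 = 0.755, a difference of about 25.5 points and an OR of 0.755/0.245, about 3.1.

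**6. Near matches.** Each needs something the article does not state. An unpooled two-sided calculation for 50% against 75% (OR 3.0) gives 55 per group: (1.960 + 0.842)² × 0.4375/0.0625 = 54.9. A one-sided log-OR calculation for OR 2.0 gives 110, but per group: (1.645 + 0.842)² / (ln 2)² × (4 + 4.5) = 109.4. Neither can be taken as what was done.

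**The case against.** The strongest defence is that 33% was meant as a relative increase, since 66.7/50 = 1.33. That may well be how the slip arose. It does not rescue the text, which calls the difference absolute and adds 33 to 50 to reach 83. No other part of the article gives a control proportion or definition that would make the sentence true.

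Other objections limit the point, and they stand:

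- A reader might infer that the article sets two rival thresholds of relevance. It does not. Only the OR of 2.0 is named as the smallest relevant effect; the 33 points are a faulty conversion of it, and the 83% is conditional on the assumed 50%.
- A reader might infer that the primary result will be judged against the wrong yardstick. The Statistical analysis section contains no relevance margin or decision rule, and the logistic model estimates the OR whatever the conversion says. Allocation, data collection and the planned test are unaffected.
- A reader might infer that policy makers will be promised twice the real effect. The 33% and 83% appear only under Sample size. The Abstract speaks of giving policy makers information on cost-effectiveness and utility, not these figures.
- Correcting the two percentages alone would leave an OR of 2.0, 50% against 66.7%, 110 participants and 80% power side by side. That combination is also false, so the repair has to reach the power statement.

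**Conclusion.** The point holds. The conversion is false at every control proportion. At the article's own 50% it overstates the difference by about a factor of two (33 against 16.7 points) and the intervention proportion by about 16 points (83% against 66.7%). More important, 55 per group match neither the OR of 2.0 (about 42% power) nor 50% against 83% (about 97%). With a 50% control proportion they give 80% power for about 50% against 75.5%.

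The conversion rests on arithmetic alone. The power figures assume a two-sided 5% test, 55 analysed per group and an unadjusted comparison. One-sided testing raises power for the OR of 2.0 to about 55% and does not reconcile the figures. Which inputs the software run used cannot be told from the article. The error does not bias the planned analysis. It misstates the target effect and the power for a primary outcome, and it should be corrected before results are known.

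**What to change.** In the Sample size section:

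1. Replace the conversion with: *At a control RTW proportion of 50%, an OR of 2.0 corresponds to 66.7% in the intervention group, an absolute difference of 16.7 percentage points.* Delete the expectation of 83% or more.
2. State which effect, control proportion and sidedness were entered in G*Power to obtain 110.
3. Restate what 55 per group deliver: either the power for an OR of 2.0 from 50% (about 42%, two-sided) or the effect detectable with 80% power (about 25.5 points, OR about 3.1).

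Optionally, report a risk difference with its 95% confidence interval beside the OR. A logistic model does not give this directly; it is obtained by standardisation over the fitted model.

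The cost is a few rewritten sentences and a look at the saved software settings. No additional patients, visits or design changes are needed. The downside is a less favourable stated power.
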